**Ethics Statement:**

The study will be conducted in accordance with the *National Statement on Ethical Conduct in Human Research* (2007) ([Link to National Statement](https://www.nhmrc.gov.au/about-us/publications/national-statement-ethical-conduct-human-research-2007-updated-2018)) , the *CPMP/ICH Note for Guidance on Good Clinical Practice* ([Link to CPMP/ICH](https://www.tga.gov.au/publication/note-guidance-good-clinical-practice-july-2000) ) and consistent with the principles that have their origin in the Declaration of Helsinki. Compliance with these standards provides assurance that the rights, safety and well-being of trial participants are respected.

| **Protocol Title** | An Audit of Savi Scout ® Radar localization for non-palpable breast lesions |
| --- | --- |
| **Objectives** | The primary objectives of iBRA-net Study are:   - To evaluate the efficacy of localization of non-palpable breast lesions with Savi Scout ®. - To establish the efficacy of axillary node marking with Savi Scout ®.   The secondary objectives are:   - To compare the efficacy of Savi Scout ® with hookwire locations of non-palpable breast lesions. |
| **Study design** | Prospective Audit |
| **Planned sample size** | 1000 (worldwide), 50 (COBL) |
| **Selection criteria** | All patients over the age of 18 electing to undergo a breast conserving localization procedure or axillary nodal marking using the Savi Scout ® System will be eligible for inclusion. |
| **Study Procedure** | Potential participants will be identified prospectively by consultant surgeons. Simple demographic, procedure and process data will be contemporaneously collected for each participant. Data will be recorded in an anonymized format using a unique alphanumeric study identification number on a secure web-based database (REDCap) designed by Vanderbilt University and hosted by Manchester University NHS Foundation Trust/Manchester University. |
| **Statistical considerations** | Power Calculation - with n=1000 patients per group, the upper limit of the observed one-sided 95% confidence interval for the difference between failure rates (seed vs wire) is expected to be less than 0.9% with 80% power, assuming the two methods both have an expected failure rate of 0.6%. Hence, if a 0.9% difference is considered an acceptable equivalence margin (eg. 0.6% for wire and 1.5% for seed), 1000 patients per group should be sufficient to establish equivalence. Simple summary statistics will be calculated for each outcome and regression analysis used to control for predictive variables. Data will be tested for distribution and differences between groups using unpaired t-tests, Mann-Whitney U tests and Chi squared tests as appropriate, based on recruitment. |
| **Time Period of Data Collection** | May 2023 – May 2024 |
| **Duration of the Study** | 1 year |

**SUMMARY**

[if applicable:] Protocol Version Control box

| **Protocol**  **Version Number** | **Date** | **Summary of Changes** |
| --- | --- | --- |
|  |  |  |
|  |  |  |
|  |  |  |
|  |  |  |

### **1. BACKGROUND AND INTRODUCTION**

1.1. DISEASE BACKGROUND

Excision of impalpable breast lesions is usually directed by preoperative wire placement into or adjacent to the target lesion, although there is a move towards using more practical devices which require intra-operative detection, such as Iodine (^125^I) radioactive seed localization, Magseed® (detectable magnetic field), the SAVI Scout® (radar technology) and the LOCalizer™ Radiofrequency Identification (RFID) System. Wire localization presents several challenges, including wire displacement, difficulty in discerning the position of the tip of the wire intraoperatively, and in some cases a long distance between wire entry point and lesion^1^. These make optimal incision placement a challenge and lead to extensive dissection to remove the target lesion, and potential failure of localisation. Wire placement occurs on the day of surgery, which can cause logistic issues for radiology and surgery departments, and lead to delays in the operating theatre. However, wires remains the default method of localization due to the limitations of other methods of localization and given the long term data supporting its effectiveness^2^.

Iodine (^125^I) radioactive seed localization has been used in some units, and has some logistical advantages^3^, however, the radiation safety precautions required to set up and support this service limits its widespread implementation^4^. Radio-occult lesion localization (ROLL) has also been used, but offers less logistical advantage compared to seeds, as it still requires radioisotope injection to occur within 24 hours of surgery. Unless contrast is also given, ROLL does not offer the surgeon mammographic or ultrasound confirmation of the site of injection in relation to the lesion^5^. Radioactive seed localization and ROLL are equally reliable to wire localization^2^.

As an alternative to wire localization, the US Food and Drug Administration (FDA) approved a new device for localizing nonpalpable breast lesions in 2014. Savi Scout® (Cianna Medical, Merit Medical Systems, Inc. South Jordan, UT) is a wireless, nonradioactive, wave reflection implant system that enables surgeons to safely and accurately remove breast tissue. The implantable 12 x 1.6mm electromagnetic wave reflector is inserted into the breast lesion under radiological guidance. The SSL system involves the insertion of the electromagnetic wave reflector into the target tissue using a sterile 16-gauge introducer needle delivery system (available needle lengths of 5, 7.5 and 10 cm) under mammogram or ultrasound guidance. The reflector is activated by infrared light impulses generated by the console probe and uses two antennas to reflect an electromagnetic wave signal back to the handpiece. The signal is processed by the console to produce an audible and visual distance to target feedback to the operator, guiding the removal of the lesion throughout surgical dissection. The detector has “insignificant MRI bloom”, displays the real-time measurement of lesion location during use, and has an alleged accuracy of ±1 mm (Cianna Medical). Savi Scout has been used in US sites since its FDA approval with several publications outlining its efficacy. Tingen et al 2020 published a retrospective review of single institution cases comparing 175 wire localisations and 320 Savi Scout ®. They have shown Savi Scout ® to be effective at localising lesions with a lower re-excision rate in the Savi Scout ® group vs the wire (5.3% vs 13.7%). These single institution series are useful but are prone to bias and limited in their usefulness for adoption of the technique amongst inexperienced users. Savi Scout® was CE marked for use in Europe in 2020 and early data is emerging from European users^6^. Systematic review of 11 studies of Savi Scout® includes 842 Savi Scout® reflectors^6^. Of these, 839 were successfully placed and 836 were successfully retrieved using SSL. This gives a successful deployment rate of 99.64% and a successful retrieval rate of 99.4%. Of the 839 successfully placed reflectors, 624 were inserted in malignant lesions with 80 requiring re-excision. The re-excision rate was therefore 12.8%. Across the four studies directly comparing Savi Scout® to wire-guided localisation, 545 WGLs were performed, and 264 reflectors were placed to localise malignant lesions. Of these, 115 WGLs required re-excision compared to 34 SSLs. This gives a re-excision rate of 21.1% for WGL and 12.9% for SSL. A chi-square test found this difference to be statistically significant (χ2 with Yates' correction=7.4639, p<0.01). This emerging data demonstrates that Savi Scout® can be used to localise breast lesions and may reduce re-excision rates. The quality of the systematic review is dependent on the quality of the datasets. We know from the introduction of any new device that it takes time for the team to learn and adopt and to get the best out of the device. Prospective data collection amongst new sites enables us to collate accurate information on outcomes and compare to existing technologies and to enable learning as a group. Larger data sets also enable us to limit the effect of confounders and bias and the limitations of retrospective data collection.

Savi Scout® is also being used for axillary nodal identification, with one published study of 23 patients demonstrating feasibility with a nodal retrieval rate of 100%^7^.

1.2. RATIONALE FOR PERFORMING THE STUDY

This study is being performed to evaluate the efficacy of Savi Scout® in localising non-palpable breast lesion and axillary marking. The majority of studies of evaluating Savi Scout® localisation in impalpable breast lesions have had small and retrospective in design. Hence the use of a prospective large multi-centre cohort enables analysis of the benefits of this usage of Savi Scout® with a higher level of evidence . De-escalation of axillary surgery reduces treatment morbidity but depends on effective methods of nodal localisation^8-13^. There is very limited evidence for the use of Savi Scout® in axillary nodal identification. A large prospective dataset will assist in appraisal of the efficacy of Savi Scout® for this purpose.

**2. HYPOTHESIS**

Savi Scout® is an accurate, safe method of localising impalpable lesions and axillary nodes.

**3. STUDY OBJECTIVES / AIMS**

3.1. PRIMARY OBJECTIVES

- - 1. To evaluate the efficacy of localization of non-palpable breast lesions with Savi Scout ®.
    2. To establish the efficacy of axillary node marking with Savi Scout ®.

3.2. SECONDARY OBJECTIVES

To compare the efficacy of Savi Scout ® with hookwire locations of non-palpable breast lesions.

**4. STUDY DESIGN**

4.1. DESIGN / STUDY TYPE

The study will be a prospective audit of outcomes related to localisation with Savi Scout ®.

4.2. EXPECTED PARTICIPANT NUMBERS

1000 globally, 50 from Chris O’Brien Lifehouse

4.3. TIME PERIOD OF THE STUDY

*:*

| **Task** | **Start Date** | **End Date** |
| --- | --- | --- |
| **Ethics Submission** | May 2023 | May 2023 |
| **Ethics Review and Approval** | Mid-May 2023 | June 2023 |
| **Advertising** | June 2023 | July 2023 |
| **Recruitment** | July 2023 | July 2024 |
| **Collection of data** | July 2023 | July 2024 |
| **Analysis of Data** | August 2024 | Sep 2024 |
| **Preparations of Reports** | Jan 2025 | Feb 2025 |
| **Publication Draft** | March 2025 | March 2025 |
| **Submission of Publications and Final Reports** | May 2025 | June 2025 |

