**6. STUDY PROCEDURES**

6.1. INVESTIGATION PLAN

The multicentre component of the trial involves a prospective audit of information relating to the use of Savi Scout®.

This involves documenting this data into a secure web-based Redcap database.

The dataset collected is the same from every international site.

There is no intervention that is carried out for the study as this is an audit.

The procedures related to Savi Scout® placement are part of normal practice and are not influenced by this study given the collection of data occurs after the decision to use Savi Scout®. Savi Scout® is an established technology for localisation of impalpable breast lesions and axillary nodes at Chris O’Brien Lifehouse.

This audit will have data contributed from multiple sites globally. The information collected will investigate the margin status of excision, accuracy of placement, timing of the placement of Savi Scout®, and the proportion of Savi Scout® placed at the time of biopsy, pathological weight of specimen, size of MRI bloom around Savi Scout® , transcutaneous detection rate, reoperation rate, complications, cancellation rate on day of surgery, reason for cancellation on day of surgery, time of day of start of surgery and identification rate of axillary nodes using Savi Scout.

Comparative analysis will be performed with the same parameters for participants that have undergone hookwire-localisation of impalpable breast lesions. Information of the hookwire-localisation cohort have been recruited from Manchester University NHS Foundation Trust/Manchester University.

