6.2. INFORMATION AND CONSENT (OR WAIVER OF CONSENT)

Those who meet the eligibility criteria will be provided with a Patient Information Sheet during one of their routine consultations with their treating surgeon. The participant will have the opportunity to discuss any questions with their surgeon before giving their consent. Those who are agreeable to participate will be asked to complete a hardcopy consent form prior to data being entered into the database. Participants would have time from their initial consult to the time of surgery which is generally 1 week to provide consent. The time to give consent will not be less than 24 hours.

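### Recruitment and data collection close in the same month (and the synopsis closes data collection earlier still), so reoperation and complications are only partly observed in late entrants

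*Protocol*

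**What the plan says.** The timetable in Protocol section 4.3 has these three rows:

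- "Recruitment | July 2023 | July 2024"
- "Collection of data | July 2023 | July 2024"
- "Analysis of Data | August 2024 | Sep 2024"

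The synopsis table gives a different period: "Time Period of Data Collection | May 2023 – May 2024". Section 4.3 places ethics submission in May 2023, and review and approval from mid-May to June 2023.

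Section 6.1 lists the outcomes, among them "transcutaneous detection rate, reoperation rate, complications, cancellation rate on day of surgery", together with margin status and the identification rate of axillary nodes. It plans a comparison on the same parameters with hookwire patients already recruited at one centre, and does not give the length of their follow-up. Section 3.2 limits the wire comparison to non-palpable breast lesions. On the time from consult to surgery, section 6.2 says: "Participants would have time from their initial consult to the time of surgery which is generally 1 week to provide consent".

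The protocol states no follow-up window for reoperation or complications, no last-surgery date for inclusion, and no rule for patients or nodes not yet operated on at closure.

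**The concern.** A patient recruited in July 2024 cannot have reoperation and complications fully observed by the end of July 2024. If events not yet seen at closure are treated as not having happened, the Savi Scout rates come out too low. Re-excision is the outcome on which the protocol's own background reports an advantage over wire (12.9% against 21.1%, section 1.1), so an undercount in the Savi Scout group alone would push the comparison in the direction already expected.

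The synopsis dates make the problem worse. Taken literally, data collection would stop while recruitment continued for two more months.

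The node objective, which is primary in section 3.1, carries a separate risk. Section 6.1 records the timing of placement and the proportion placed at biopsy, and by its title in the reference list the one cited axillary study was a series marked before neoadjuvant chemotherapy. Some markers may therefore be in place with no surgery by closure.

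**Working it through.** **The plan's own figure.** Section 8.1 says that with 1000 per group and 0.6% failure in both, the upper one-sided 95% limit of the difference falls below 0.9% with 80% power. Unpooled normal approximation: (1.645 + 0.842) × √(2 × 0.006 × 0.994 / 1000) = 2.487 × 0.003454 = 0.86%. The statement reproduces and is not disputed. It concerns localisation failure, not reoperation.

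**Inputs from the protocol.** Recruitment and data collection July 2023 to July 2024 (12 to 13 months); analysis from August 2024; surgery generally about 1 week after the initial consult; background re-excision rate for Savi Scout in malignant lesions 80/624 = 12.8%.

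**Assumptions.** Uniform accrual; data closing at the end of accrual; reoperation window *w* of 1 to 3 months, with reoperations spread evenly over it. The protocol gives none of these.

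**Incomplete follow-up and its effect.** Share of patients without the full window = *w*/12. On average these patients have half their window observed, so the share of reoperations missed is *w*/24 and the rate seen is 12.8% × (1 − *w*/24).

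| *w* (months) | Incomplete follow-up | Rate seen when truth is 12.8% |
| --- | --- | --- |
| 1 | 8% | 12.3% |
| 2 | 17% | 11.7% |
| 3 | 25% | 11.2% |

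**Sensitivity to later reoperations.** Add the 1-week lag to surgery and assume reoperation evenly over 2–6, 2–8 or 4–12 weeks after surgery. The mean delay from entry is then 5, 6 or 9 weeks. Share missed = mean delay / accrual length. Over 12 months (52.2 weeks) this is 9.6%, 11.5% or 17.2%, and 12.8% is seen as 11.6%, 11.3% or 10.6%. Over 13 months (56.5 weeks) the shares missed are 8.8%, 10.6% and 15.9%.

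**If the shared month hides a partial tail.** If recruitment stopped on 1 July and data closed on 31 July, the share missed under the same delays falls to about 2 to 9%.

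**Synopsis dates.** If data collection ended in May 2024 and recruitment in July 2024, the last two months of entrants would contribute nothing: 2/12 = 17% (2/13 = 15%).

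**Patients not yet operated on.** Breast lesions, at a lag of about 1 week: 1/52.2 = 2%. Nodes, at an assumed interval *d* from marking to surgery and with entry at marking: *d*/12, which is 25% for 3 months and 50% for 6 months.

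**The case against.** Several points on the other side are sound and limit the finding.

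- **The powered quantity.** Localisation failure is presumably known at surgery, about a week after the consult, although the protocol does not define failure. The comparison in section 8.1 is therefore probably little affected. This stands.
- **Bias against wire.** A reader might infer that Savi Scout is flattered against a fully followed wire cohort. Section 6.1 says only that the wire patients have been recruited. Their follow-up is not stated, so the direction is conditional.
- **Nodes and wire.** A reader might also take the missing node outcomes as favouring Savi Scout over wire. The wire comparison covers breast lesions only, so they cannot. Nor does the protocol say that signal weakens with time in place, so nothing can be said about which way the missing nodes would have turned out.
- **Margins.** Margin status is a single pathology result. Early closure would leave it missing, not falsely clear, and no direction of bias follows.
- **The node interval.** The 3 to 6 months is an assumption. If the 1-week interval in section 6.2 also holds for node patients, few would be outstanding. The protocol does not say when they enter.
- **Scope of the timetable.** The 4.3 table includes ethics submission and advertising and may describe the local site, which expects 50 of the 1000 patients. It is not labelled either way. If it is local, the percentages apply to those 50.
- **Left to an analysis plan.** Windows and handling rules can be set there. An analysis plan cannot recover events that the protocol's schedule stops collecting, so this does not answer the point.

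**Conclusion.** The concern holds in a limited form. As scheduled, reoperation and complications are incompletely observed in late entrants, and the two statements of the data collection period conflict at both ends.

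Under uniform 12-month accrual and a window of 1 to 3 months, 8 to 25% of patients have incomplete follow-up. A true re-excision rate of 12.8% would appear about 0.5 to 1.6 points too low, or up to about 2.2 points (12.8 − 10.6) with later reoperations. That is modest beside the background difference of 8.2 points (21.1 − 12.9), but it is avoidable. The protocol gives no background complication rate, so no size is put on that outcome.

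These figures assume that unseen events are counted as absent. Whether the undercount favours Savi Scout over wire depends on the wire cohort's follow-up and is not shown. The node problem is one of missing outcomes for a primary objective. It could be as large as 25 to 50% if marking precedes surgery by 3 to 6 months, and small if it does not.

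**What to change.** 1. Reconcile the data collection dates in the synopsis with section 4.3, including the start relative to ethics approval, and say whether the 4.3 timetable is local or global.
2. In section 4.3, let outcome collection run past the last enrolment, for example to the end of October 2024, with analysis in November and December. Section 4.3 shows no task from October to December 2024, so this fits before the reports in January 2025. A November close would push a two-month analysis into January.
3. Analyse reoperation and complications over one fixed window from index surgery, in patients who have completed it, and apply the same window to the wire cohort. From the end of July to the end of October is about 13 weeks. Less the 1 week to surgery, that leaves room for a window of about 12 weeks in the last entrants.
4. Report the number of markers, breast and node separately, not yet operated on at closure.

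The cost is that analysis starts about three months later and sites enter outcomes for that much longer. The extension does not clear every node. At an assumed 6-month interval, (6 − 3)/12 = 25% would still be outstanding, and these must be reported as such.

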4.4 ENDPOINTS

PRIMARY ENDPOINTS

Savi Scout ®is an accurate method of identifying non-palpable breast lesion.

SECONDARY ENDPOINTS

Savi Scout ®is an accurate method of identifying axillary nodes.

**5. STUDY PARTICIPANTS**

5.1. INCLUSION CRITERIA

Patients undergoing a breast conserving localization procedure or axillary nodal marking using the Savi Scout ® System.

18 years of age

Willing to participate in the study.

5.2. EXCLUSION CRITERIA

Pregnancy

Unable to read and write English to a level required for consent and completion of written questionnaires.

Unwilling to provide consent.

5.3 KEY ELEMENTS OF RECRUITMENT (AS PER NS)

1. Participants who have decided to have their localisation carried out with Savi Scout will be recruited for the study.

2. Participants will be identified by treating clinician. They will be given the option to have information regarding their localisation included into the prospective database.

3. There will be no impact in the relationship between researcher and potential participant as the participant will go ahead with their procedure regardless of their involvement in the study.

4. The participants will be verbally informed of what the study entails and they will be given a patient information sheet prior to making their decision. The participant will be able to ask questions from the researcher after having time to read the patient information sheet.

5. Given that this is audit of information regarding their treatment, there is no risk to the patient or for the viability of the project.

5.4 CONFOUNDERS

5.5 STUDY LIMITATIONS

Given that this is a multi-centre study, there will be differences in the radiologist’s technique in placing the Savi Scout® localisation device and the surgeon’s technique in retrieving the targeted lesion.

This may mean that if a particular group has a large contribution to the dataset, the results may be skewed.

This study is a prospective audit and does not have the same level of evidence as a randomised controlled trial.

**6. STUDY PROCEDURES**

6.1. INVESTIGATION PLAN

The multicentre component of the trial involves a prospective audit of information relating to the use of Savi Scout®.

This involves documenting this data into a secure web-based Redcap database.

The dataset collected is the same from every international site.

There is no intervention that is carried out for the study as this is an audit.

The procedures related to Savi Scout® placement are part of normal practice and are not influenced by this study given the collection of data occurs after the decision to use Savi Scout®. Savi Scout® is an established technology for localisation of impalpable breast lesions and axillary nodes at Chris O’Brien Lifehouse.

This audit will have data contributed from multiple sites globally. The information collected will investigate the margin status of excision, accuracy of placement, timing of the placement of Savi Scout®, and the proportion of Savi Scout® placed at the time of biopsy, pathological weight of specimen, size of MRI bloom around Savi Scout® , transcutaneous detection rate, reoperation rate, complications, cancellation rate on day of surgery, reason for cancellation on day of surgery, time of day of start of surgery and identification rate of axillary nodes using Savi Scout.

Comparative analysis will be performed with the same parameters for participants that have undergone hookwire-localisation of impalpable breast lesions. Information of the hookwire-localisation cohort have been recruited from Manchester University NHS Foundation Trust/Manchester University.

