**8. STATISTICAL CONSIDERATIONS**

8.1. SAMPLE SIZE OR POWER CALCULATION

Power Calculation - with n=1000 patients per group, the upper limit of the observed one-sided 95% confidence interval for the difference between failure rates (seed vs wire) is expected to be less than 0.9% with 80% power, assuming the two methods both have an expected failure rate of 0.6%. Hence, if a 0.9% difference is considered an acceptable equivalence margin (eg. 0.6% for wire and 1.5% for seed), 1000 patients per group should be sufficient to establish equivalence.

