8.2. PROVIDE A DETAILED ANALYSIS PLAN

Simple summary statistics will be calculated for each outcome and regression analysis used to control for predictive variables. Data will be tested for distribution and differences between groups using unpaired t-tests, Mann-Whitney U tests and Chi squared tests as appropriate, based on recruitment.

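### The hookwire comparator reads as an already-recruited Manchester cohort set against prospective Savi Scout cases worldwide, so the planned regression cannot isolate the device effect and the pooled contrast cannot by itself establish equivalence

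*Protocol*

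**What the plan says.** Section 3.2 makes it a secondary objective to compare the efficacy of Savi Scout "with hookwire locations of non-palpable breast lesions". Section 8.1 rests the whole sample size on that comparison: 1000 patients per group, 0.6% failures expected with either method, a margin of 0.9 percentage points, a one-sided 95% confidence limit and 80% power.

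The two groups come from different places:

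- **Savi Scout.** Section 5.3: "Participants who have decided to have their localisation carried out with Savi Scout will be recruited for the study". Section 6.1: "This audit will have data contributed from multiple sites globally". The recruitment row in section 4.3 reads "July 2023 | July 2024". The synopsis dates data collection May 2023 to May 2024, which is also forward-looking.
- **Hookwire.** Section 6.1 compares these cases, on the same parameters, with "participants that have undergone hookwire-localisation of impalpable breast lesions", and adds: "Information of the hookwire-localisation cohort have been recruited from Manchester University NHS Foundation Trust/Manchester University". No dates, size or eligibility rule are given for this cohort, and no concurrent wire recruitment is described.

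For adjustment, section 8.2 offers "regression analysis used to control for predictive variables" and unpaired tests. No centre or period term is named. Section 5.4 (Confounders) is a heading without text. Section 5.5 mentions differences in technique between sites and the lack of randomisation, but not the separate source of the comparator.

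**The concern.** A comparison against a 0.9-point margin around a 0.6% failure rate is sensitive to small systematic differences. If the wire cases come from one institution and an earlier time, any observed difference in failure, or its absence, may reflect who operated, where and when. The protocol itself expects such effects: section 5.5 says radiologist and surgeon technique will vary between sites, and section 1.1 says teams need time to learn a new device and refers to data from new sites.

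This is more than a detail for a statistical analysis plan. Such a plan can name covariates, but it cannot supply wire cases at sites that have none, or wire cases from the Savi Scout period. At stake is whether meeting the margin could be read as equivalence of the devices.

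**Working it through.** **Inputs.** From section 8.1: p = 0.006 in both groups, margin m = 0.009, n = 1000 per group, one-sided 95% limit (z = 1.645), 80% power (z = 0.842). The size of the wire cohort is not stated, so 1000 is taken from section 8.1. The centre or period shifts and the numbers of same-site Savi Scout cases below are assumptions, because the documents give none.

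**1. The plan's own figure.** With unpooled standard error SE = √(2 × 0.006 × 0.994 / 1000) = 0.003454:

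- Margin reachable with 80% power: (1.645 + 0.842) × 0.003454 = 0.0086, or 0.86 points, which is below 0.9.
- Power at 0.9 points: Φ(0.009 / 0.003454 − 1.645) = Φ(0.961) = 83%.
- Number needed for 80%: 911 per group.

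The arithmetic in section 8.1 holds. Its hidden assumption is that the groups differ only by device.

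**2. No true device difference, but a shift s in the Savi Scout group.** Chance of meeting the margin = Φ((0.009 − s) / SE − 1.645), with SE = √{[(0.006 + s)(0.994 − s) + 0.006 × 0.994] / 1000}.

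| Shift s (points) | SE | Chance of meeting the margin |
|---|---|---|
| 0 | 0.00345 | 83% |
| 0.2 | 0.00373 | 59% |
| 0.3 | 0.00386 | 46% |
| 0.5 | 0.00410 | 25% |

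The pattern does not depend on the normal approximation. Exact power with a Newcombe limit falls from 78% to 54%, 42% and 23% for the same shifts.

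**3. Savi Scout truly worse by the full margin (1.5% against 0.6%), with the wire rate raised by t.** The observed difference is then 0.009 − t, so the chance of wrongly meeting the margin = Φ(t / SE − 1.645), with SE = √{[0.015 × 0.985 + (0.006 + t)(0.994 − t)] / 1000}.

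| Shift t (points) | SE | False equivalence |
|---|---|---|
| 0 | 0.00456 | 5% |
| 0.2 | 0.00477 | 11% |
| 0.3 | 0.00487 | 15% |
| 0.5 | 0.00507 | 26% |

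**4. What regression can separate.** Take Manchester plus, for illustration, 10 other sites. A model with an intercept, a device term and 10 centre terms has 12 parameters.

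- If Manchester supplies only wire cases and the others only Savi Scout cases, the design matrix has rank 11. The device effect cannot be estimated apart from centre.
- If Manchester supplies both, the rank is 12, but only Manchester's Savi Scout cases inform the centre-adjusted contrast. With k such cases against 1000 wire cases, SE = √{0.006 × 0.994 × (1/1000 + 1/k)} and power = Φ(0.009 / SE − 1.645).

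| k | SE | Power for 0.9 points |
|---|---|---|
| 50 | 0.01119 | 20% |
| 100 | 0.00810 | 30% |
| 200 | 0.00598 | 44% |

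Expected failures among these k cases are 0.3, 0.6 and 1.2, so the normal approximation is rough here and the percentages are indicative only.

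**5. Period.** If every wire case precedes every Savi Scout case, an indicator for early against late is the same column as device. No covariate list separates the two, even within Manchester.

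**The case against.** The strongest reply is that the comparison is only a secondary objective of a self-described audit, that section 5.5 already ranks the evidence below a randomised trial and warns of site differences, and that much of the confounding is inferred. Much of this limits the point:

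- **Centre.** A reader might infer that device and centre are wholly inseparable. That is not shown. The contents list a section 4.5 on study sites, whose text was not available for this review, and it may say that Manchester or other sites use both devices.
- **Source.** Manchester also hosts the database (section 9), so the sentence in section 6.1 could mean that Manchester supplied the data rather than treated every patient.
- **Period.** An earlier period rests on verb tense alone.
- **Entry rule.** A reader might infer that wire cases cancelled before insertion are excluded by definition, making that cancellation rate zero. The phrase "participants that have undergone hookwire-localisation of impalpable breast lesions" is not an eligibility rule, and the same sentence promises the same parameters, which include day-of-surgery cancellation. The entry rule is unclear, no more.
- **Model.** A reader might object to an odds ratio or to too few events for a logistic model. Section 8.2 names no model form, and that choice may properly sit in an analysis plan.

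What remains is that the plain text sets one completed cohort from one named source against prospective worldwide cases, builds a formal margin claim on the contrast, and never names the separate source of the comparator as a limitation.

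**Conclusion.** The point stands in a conditional form. On the plain reading of section 6.1, device is confounded with period, and with centre wherever a site has no wire cases. The regression in section 8.2 cannot undo this. If Manchester has no Savi Scout cases, a centre-adjusted device effect cannot be estimated. If it has an assumed 50 to 200, power for the margin is only about 20% to 44%, and period remains confounded.

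A shift of 0.2 to 0.3 points, one third of the margin or less, is enough to change the conclusion materially in either direction. These shifts are illustrations, not estimates of the real bias.

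The defect does not extend to the sample-size arithmetic or to the two primary objectives in section 3.1, which concern Savi Scout alone. It limits what the secondary comparison and the equivalence statement can support. It should be fixed, but it does not invalidate the study.

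**What to change.** 1. In sections 6.1 and 8.2, pre-specify a comparison restricted to Manchester and any other site that supplies both devices. Report it as a risk difference with its confidence interval, beside the pooled comparison.
2. In sections 8.1 and 8.2, state that the pooled contrast is descriptive and does not by itself establish device equivalence, whether or not the two comparisons agree. Agreement with an imprecise same-site contrast that may still be confounded by period would not validate the pooled result. If no site supplies both devices, say that only the descriptive comparison remains.
3. In section 6.1, record the wire cohort's treating sites, dates and entry rule. In sections 5.4 and 5.5, name confounding by centre and period. Compare day-of-surgery cancellation and placement failure between groups only if the wire cohort was assembled by intended localisation method.

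Adjustment or weighting for case mix is no substitute, because it does not address centre or period.

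The cost is wording and analysis work, with no change to patient procedures. The price is an imprecise same-site estimate and a more cautious comparative claim.
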